# The use of digitally collected patient-reported outcome measures for newly operated patients with total knee and hip replacements to improve post-treatment recovery: study protocol for a randomized controlled trial

**DOI:** 10.1186/s13063-020-04252-y

**Published:** 2020-04-09

**Keywords:** Health-care policy, PROM, Quality of care, TKR, THR, Value-based health care, Randomized controlled trial

## Abstract

**Background:**

The number of total knee replacements (TKRs) and total hip replacements (THRs) has been increasing noticeably in high-income countries, such as Germany. In particular, the number of revisions is expected to rise because of higher life expectancy and procedures performed on younger patients, impacting the budgets of health-care systems. Quality transparency is the basis of holistic patient pathway optimization. Nevertheless, a nation-wide cross-sectoral assessment of quality from a patient perspective does not yet exist. Several studies have shown that the use of patient-reported outcome measures (PROMs) is effective for measuring quality and monitoring post-treatment recovery. For the first time in Germany, we test whether early detection of critical recovery paths using PROMs after TKR/THR improves the quality of care in a cost-effective way and can be recommended for implementation into standard care.

**Methods/design:**

The study is a two-arm multi-center patient-level randomized controlled trial. Patients from nine hospitals are included in the study. Patient-centered questionnaires are employed to regularly measure digitized PROMs of TKR/THR patients from the time of hospital admission until 12 months post-discharge. An expert consortium has defined PROM alert thresholds at 1, 3, and 6 months to signal critical recovery paths after TKR/THR. An algorithm alerts study assistants if patients are not recovering in line with expected recovery paths. The study assistants contact patients and their physicians to investigate and, if needed, adjust the post-treatment protocol. When sickness funds’ claims data are added, the cost-effectiveness of the intervention can be analyzed.

**Discussion:**

The study is expected to deliver an important contribution to test PROMs as an intervention tool and examine the determinants of high-quality endoprosthetic care. Depending on a positive and cost-effective impact, the goal is to transfer the study design into standard care. During the trial design phase, several insights have been discovered, and there were opportunities for efficient digital monitoring limited by existing legacy care models. Digitalization in hospital processes and the implementation of digital tools still represent challenges for hospital personnel and patients. Furthermore, data privacy regulations and the separation between the in- and outpatient sector are roadblocks to effectively monitor and assess quality along the full patient pathway.

**Trial registration:**

German Clinical Trials Register: DRKS00019916. Registered November 26, 2019 – retrospectively registered.

## Background

Total knee replacements (TKRs) and total hip replacements (THRs) are among the most frequent and increasing surgeries in high-income countries, such as Germany. They are considered to be effective but also highly invasive procedures to treat osteoarthritis in the knee and hip. In 2016, in Germany, there were more than 187,000 procedures (230 per 100,000 population) for TKRs – a 38% increase compared with 2006 – and 233,000 procedures (280 per 100,000 population) for THRs – a 17% increase compared with 2006 [1–3]. Moreover, the number of primary as well as revision procedures is expected to rise steadily because of increased life expectancies and procedures performed on younger patients [2]. This development has a significant impact on the budgets of health-care systems. Measuring patient-reported quality helps to generate transparency, to evaluate treatments, and as a consequence to optimize patients’ pathways (indication, procedure, and recovery), leading to enlarged revision horizons and a decreased number of revisions [4].

Quality of joint replacement in Germany is measured and monitored by several mandatory or voluntary initiatives. They concentrate on the collection and analyses of clinical quality indicators and administrative data as well as the adherence to structural and processual standards and the interpretation of medical documentation [5]. These quality initiatives are limited mostly to the acute inpatient sector [6]. A nation-wide standardized and cross-sectoral assessment of quality from a patient perspective does not exist yet. As a result, the improvement of arthroplasty-relevant problems such as post-operative joint functionality, pain, or constraints in daily life cannot be assessed by the existing quality measurement tools. However, an improvement in those quality dimensions defines treatment success [7] and significantly affects patient utility [8]. Consequently, a recent study in the UK concluded that, for patients with THR, quality measured by patient-reported outcomes (PROMs) significantly affects patient utility in the form of willingness to travel and hospital demand positively. In contrast, existing quality indicators such as mortality rates or readmission rates have either only a small positive or even insignificant effect [8].

Furthermore, increased transparency of the patients’ recovery process using PROMs initiates a direct feedback mechanism between physician and patient, thus optimizing surgeries [9, 10] and best practice sharing [7]. At present this is barely given. After rehabilitation, patients will seldom return to the hospital for follow-up visits and instead they see their family physicians or outpatient specialists. Unfortunately, communication channels between hospitals and follow-up physicians are often not present, preventing any feedback mechanism regarding their patients’ recovery process [11].

For example, the effects of improved medical quality by continuously monitoring patients after surgery using PROMs have been concluded in a study of patients with cancer [12, 13]. The study shows that, during routine treatment, constant monitoring and early detection of critical recovery paths via PROMs significantly improved survival rates and decreased the number of emergency visits [12, 13].

Our study is designed to go beyond testing the effectiveness of PROMs as a quality measurement instrument. For the first time in Germany, we want to test whether an early detection of critical recovery paths after TKR/THR via PROMs and change of post-treatment pathways improves clinical quality indicators such as readmissions and patient-centered quality measures such as health-related quality of life and joint functionality and, in turn, leads to a decrease of health-care costs. The study focuses on two specific questions: (a) Can the use of PROMs after TKR/THR impact the patient pathway in a positive and cost-effective manner? (b) Can we recommend the implementation of PROMs into standard care, and what are best practices to follow?

## Methods/Design

### Overall study design

This study is a two-arm multi-center patient-level randomized controlled trial (RCT). Patient-centered questionnaires are employed digitally to regularly measure PROMs of patients with TKR and THR from the time of hospital admission until 12 months after discharge. With the support of an expert consortium of physicians, PROM threshold alert values at 1, 3, and 6 months have been defined to signal critical recovery of patients after TKR/THR. With the help of an algorithm, patients and post-treatment physicians are alerted to intervene in case of critical PROM values.

By adding cross-sectoral insurance claims data (resource consumption: drugs, physiotherapy, specialist visits, complications, infections, and hospital stays) at the patient level, the study examines the effect of PROM-based monitoring of patients up to 12 months post-surgery on the clinical as well as patient-reported outcomes and its cost-effectiveness.

### Ethics, consent, permissions, and funding

The study is funded by the Innovation Fund of the German Federal Joint Committee (G-BA) in the stream “Care models with comprehensive and measurable results and process responsibility”. The funding period is set between April 1, 2019 and March 31, 2023. The study will be conducted in accordance with the Declaration of Helsinki. The study was approved primarily by the Charité’s Ethic Committee, Berlin (EA4/169/19). The other responsible ethical review committees of participating hospitals (Medical Chamber Hamburg, Medical Chamber Schleswig-Holstein, Hannover Medical School, Friedrich-Schiller University Jena, and Medical Chamber Brandenburg) agreed with the decision. The study is registered at the German Clinical Trials Register (DRKS) under trial number DRKS00019916. All potentially eligible participants will be approached to offer their informed consent to participate in the study. The current protocol is version 1, dated January 15, 2020. Any changes in the study design will be communicated to all project partners, including hospitals.

### Study setting

The study started on October 1, 2019 and will last for two years, whereas patient recruitment will end after one year, on September 30, 2020. The second year will concentrate on follow-ups and corresponding interventions. After two years, the study will be evaluated by an independent and impartial research institute (aQua Institute, Göttingen, Germany). Study centers are the nine participating hospitals. These hospitals are located around Germany (seven different federal states) and are among Germany’s leading endoprosthetic centers. Hospitals differ in their type, including university hospitals, specialized endoprosthetic centers, full-service providers, and specialist outpatient clinics.

Based on historical hospital case volumes for elective TKR/THR to estimate expected workload, up to two study assistants are employed at each center – funded by means of the Innovation Fund – to operationalize the study design in each center. Before the start of the project, these study assistants were trained thoroughly in workshops to be in line with the specifications of the study design. The study assistants are responsible for all study-related activities during the patients’ hospital stay and for follow-up as well as the initiation and documentation of interventions and a complete final documentation of the participant after 12 months.

The study assistants and patients use a software interface provided by HRTBT Medical Solutions GmbH (Berlin, Germany), a digital solutions provider for hospitals, to document patient enrollment, key procedure aspects, and the patient-reported outcomes. Patients’ health procedure and claims data along the care pathway are accessed via the participating German sickness funds BARMER and BKK, both of which are part of the social health insurance scheme [14]. These insurance claims data will be extracted for four years (2018–2021) for those patients insured in one of these funds and having consented to study design and data sharing.

### Sample size

The estimation of the study’s sample size is based on historical case volumes (identified by procedure codes OPS 5–820 and 5–822) of the nine study hospitals from 2018. Hence, we expect around 17,500 patients to be eligible in the 12-month recruiting time frame. This figure already excludes emergency patients and minors. Furthermore, prior field studies by HRTBT Medical Solutions GmbH suggest that around 15% of patients reject participation and around 30% of the remainder will not finalize all follow-up surveys despite reminders and active follow-up efforts. Consequently, we expect to reach a sample size of around 10,500 participants having completed all follow-ups. This number is not yet adjusted for people without direct or indirect access to the internet or other technical constraints, but increasing case volumes compared with 2018 are expected to balance this effect.

Furthermore, it is expected that insurance claims data for patients insured in the two participating sickness funds (about 2700 patients) can be obtained, resulting in a sample size of 2700 for our primary endpoint. If we assume a statistical difference in effect between the intervention and control groups of 0.15 standard deviations, an error probability of less than 5%, and a power of 80%, a sample size of only around 1400 patients with insurance claims data is required for analysis.

### Eligibility criteria

Eligible for this study are all patients with primary elective TKR and THR above the age of 18 having a scheduled surgery or pre-surgery visit between October 2019 and September 2020. Exclusion criteria for participation are emergencies (e.g., femoral fracture), patients with American Society of Anesthesiologists classification 4–6 (4: a patient with a life-threatening disease, 5: a moribund patient who is unlikely to survive without surgery, 6: a deceased patient with confirmed brain death or an organ donor), and patients younger than 18 years. Additionally, for practical reasons, patients without direct or indirect access to an e-mail account are excluded from the study. E-mail addresses from relatives are accepted. All patients who deny participation will not be included in the study.

### Informed consent

All patients with a primary elective TKR or THR will be approached by their corresponding study assistants for a patient briefing once they have been scheduled for surgery in the corresponding hospital. Patients will be informed by either the study assistant or the corresponding physicians of the study and its benefits, risks, and design. Additionally, they are handed a comprehensive study information document. Before patients are included, they are required to sign an informed consent form for their study participation (Supplement 1). The informed consent allows us to contact the patient via e-mail, post, and telephone and to process and link the patient’s data from different sources during and after the study.

Patients are asked to sign two additional consent forms: (a) one for processing their hospital administrative data and (b) one for processing their insurance data in case the patient is contracted with one of the participating sickness funds. Both of these consent forms are optional and are not required to participate in the study.

Patients will be free to withdraw from either one of the three consents without stating a reason. If the patients withdraw from the consent for participation, all their data will be deleted. Patients are allowed to participate in other studies as long as these do not interfere with our study.

### Participant timeline

Each participant will be participating in the study for a maximum of 12 months plus the duration of the hospital stay, starting with the admission day followed by the inpatient stay and the discharge and post-discharge period. The participant will have to answer two questionnaires during the hospital stay: at admission and discharge. At discharge, the randomized allocation into the intervention and control groups takes effect, and the participant is followed up with electronic questionnaires either one or four times in the 12 months after hospital discharge. With the final questionnaire after 12 months, the study will conclude for each participant regardless of allocation. The timeline for the participants is presented in Fig. 1.

**Fig. 1 Fig1:**
[figure not shown]
Standard protocol items – PROMoting Quality

### Baseline assessment

Baseline assessment takes place for all eligible participants at the day of admission into the hospital. The timing differs slightly between the study centers. Three study centers perform the baseline assessment during their pre-surgery examination days; this can be up to 6 weeks before surgery. After giving informed consent, the participant will be included in the study by providing name and e-mail address. In the next step, while waiting for the physician’s appointment, the participant is given a tablet to respond to a 10- to 15-min questionnaire consisting of basic demographic, comorbidity information, and selected PROM sets.

The overall questionnaire is based on the ICHOM (International Consortium for Health Outcomes Measurement) Standard Set for Hip and Knee Osteoarthritis, which consists of the EQ-5D-5L, HOOS-PS/KOOS-PS, and an analogue pain scale. This set was refined by adding the PROMIS Depression and Fatigue sets, as studies show that the recovery process is also affected by patients’ mental conditions [15]. During selection of the PROM sets, three criteria were of utmost importance. First, the questionnaire should be brief to include it in the hospital’s daily activities. Second, the sets should be renowned and proven by literature. Finally, the combined set of PROMs should cover all important patient-related aspects of the osteoarthritic condition and the elective TKR and THR procedures: health-related quality of life, functionality, pain, and mental condition.

At discharge from the hospital, the participant once again is handed a tablet to complete – alone or with the help of the study assistant – a mostly identical questionnaire (omitting demographic and comorbidity questions). Besides documenting the data from the questionnaire, the study assistant will document additional parameters at admission, after surgery, and at discharge, encapsulating information on the participant’s medical history, the surgery, and aftercare. In Fig. 1, the standard protocol items at different points in time are shown.

### Randomization and blinding

The allocation of participants occurs after completion of the patient survey at the day of discharge; thus, during inpatient stay, all eligible patients are treated equally. All participants are stratified into patients with TKR or THR and then randomly allocated at a ratio of 1:1 into the intervention or control group. No further stratifications or corrections are performed. Owing to data security regulations, randomization will be carried out for each hospital individually. Figure 2 shows the randomization flow. The study’s software provider will be responsible for the randomization algorithm, and allocation will be shown to the study assistant or the physician only after discharge of the participant. Hence, during the inpatient stay, the hospital staff and the participants are blinded. The participants will stay blinded until the end of the study, not knowing whether they are in the intervention or control group. Frequency of the surveys is not disclosed to patients, in either the intervention or control group.

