### Intervention

Whereas participants in the control group will be asked to complete only a final follow-up questionnaire 12 months post-discharge, participants in the intervention group have to complete four follow-up questionnaires: at months 1, 3, and 6 and a final follow-up 12 months after discharge. All follow-up questionnaires are sent via e-mail and are answered electronically by the participants on their computers, smartphones, or tablets. In case the participants do not have an e-mail account, e-mails are sent to relatives if agreed upon and jointly filled out by relative and patient. Results from the questionnaires will be automatically transferred to the study’s software and are observable by the hospitals’ study assistants and physicians; 1-, 3-, and 6-month PROM set scores will then be screened for critical values or unfavorable developments.

When critical values or developments are detected, the software alerts the study assistants of the corresponding hospitals and an intervention is initiated. Interventions are characterized by three steps. First, the study assistant sends a standardized report to the participant, via post or e-mail, where critical values and developments are highlighted and a follow-up call is announced. Second, the study assistant calls the participants by phone to inform them of the critical values, asking permission to forward the PROM results to their outpatient specialist or general practitioner and recommending a visit to their physician to potentially adjust the treatment. Finally, a report with the participant’s results will be forwarded, by post or fax, to the outpatient physician. In the next regular questionnaire, participants are asked to report changes in their treatment schedule in order to document modifications in the outpatient physicians’ treatment with respect to physiotherapy, medication, or surgery.

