### Data quality enhancement

Each study assistant is provided with a digital dashboard showing open tasks, critical value alerts, and patients’ activity related to receiving and answering follow-up questionnaires. Each task is associated with a deadline, and a color code reminds the study assistant of open tasks. For the purpose of data completeness, the participants will be reminded by the software to fill in their follow-up questionnaires 1, 2, and 7 days after the initial follow-up questionnaires are sent out. If a participant has not completed the questionnaire after three reminders, the study assistant will call to support him or her.

Moreover, predefined standardized e-mails, guidelines for the follow-ups, and intervention calls ensure consistency between study centers. Furthermore, adherence to the protocol given in the study design was promoted in training on the ground and during a central workshop for all study assistants and physicians.

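### Participants are said to be blinded to the end, but the intervention's own contacts let them infer their arm, so reporting bias in the self-reported outcomes is not ruled out

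*Protocol article*

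**What the plan says.** The Randomization and blinding section of the protocol article places allocation after the discharge survey. For the year that follows it makes an unqualified statement: "The participants will stay blinded until the end of the study, not knowing whether they are in the intervention or control group". One safeguard is given: "Frequency of the surveys is not disclosed to patients, in either the intervention or control group". The same section says that the study assistant or physician is shown the allocation once the patient has been discharged.

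Other sections describe what participants go through:

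- Participant timeline: "the participant is followed up with electronic questionnaires either one or four times in the 12 months after hospital discharge".
- Intervention, control arm: "participants in the control group will be asked to complete only a final follow-up questionnaire 12 months post-discharge".
- Intervention, intervention arm: "participants in the intervention group have to complete four follow-up questionnaires: at months 1, 3, and 6 and a final follow-up 12 months after discharge".
- Intervention, after an alert: "the study assistant sends a standardized report to the participant, via post or e-mail, where critical values and developments are highlighted". A call is announced, and then "the study assistant calls the participants by phone to inform them of the critical values". In that call the assistant also asks to forward the results and recommends seeing a physician.
- Data quality enhancement: "If a participant has not completed the questionnaire after three reminders, the study assistant will call to support him or her".

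Under Outcomes, the quality side of the primary endpoint is a composite of PROMs and clinical measures. Function, quality of life, pain and satisfaction are secondary outcomes. The Limitations section does not mention loss of blinding.

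**The concern.** Withholding the survey schedule keeps a participant from being told the arm. It does not hide what then happens to that participant. Someone who is written to and telephoned about their own poor scores has strong evidence of being in the monitored group, and the protocol describes no matching contact for controls.

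The outcomes at stake are largely answers that these participants give about themselves. EQ-5D-5L and HOOS-PS/KOOS-PS serve both as alert triggers and as outcomes. A reader who takes the blinding statement at face value would discount differential reporting when interpreting a PROM difference between the arms, although the design does not exclude it. This matters more because the results are meant to feed a decision on German-wide implementation (Dissemination).

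**Working it through.** No calculation settles this point. It rests on setting the sections beside each other.

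**1. Contact by arm after discharge (Intervention; Data quality enhancement)**

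| Contact | Control | Intervention |
|---|---|---|
| Questionnaires | 1 (month 12) | 4 (months 1, 3, 6, 12), so 4 − 1 = 3 more |
| Screening for alerts | none | months 1, 3 and 6 |
| Report highlighting critical scores | none described | after each alert |
| Call about those scores, request to forward results, advice to see a physician | none described | after each alert |
| Reminders and a support call for non-response | yes | yes |

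Only the last row is common to both arms, and even that applies at one time point in controls and four in the intervention arm.

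**2. Can participants interpret these contacts?** Informed consent says that patients are told the study's design and receive a written information document. The wording of that document is not shown, so how clearly it describes the two arms is unknown. Limitations considers that intervention participants might learn to answer in a way that avoids interventions. That supposes they can recognise an intervention when it occurs.

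**3. How often might alerts occur?** Besides absolute thresholds, Table 1 and its footnote make any worsening of EQ-5D-5L or HOOS-PS/KOOS-PS since the previous questionnaire an alert. No alert rate is given, so the share of the arm affected cannot be stated.

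**4. Does the cue reach the outcome questionnaire?** After an alert, the next regular questionnaire asks about changes in treatment. For a month-6 alert, the next one is month 12, which is also the final outcome assessment.

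**5. Staff.** Study assistants see the allocation after discharge. They run the interventions, document the 12-month follow-up (Study setting) and call persistent non-responders to support completion. So staff who know the arm can be in contact with a participant while outcome data are being collected.

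**6. Which outcomes are exposed?** The PROM components of the primary composite are self-reported. The secondary outcomes fall into five groups: function, quality of life, pain, satisfaction, and clinical events such as revision and re-operation. The first four of the five are self-reported. Costs come from sickness-fund claims and are not.

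**7. Can the bias be sized?** No. The documents give no reporting shift, no alert rate and no direction. The one nearby figure is the planning difference of 0.15 SD. It reproduces the stated sample size: 2 × (1.960 + 0.842)² / 0.15² ≈ 698 per arm, or 1,396 against around 1,400. But Sample size attaches it to patients with claims data for the cost-effectiveness endpoint, not to a PROM score, so it is not a yardstick for bias in a PROM. The sample size is not in question here.

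**The case against.** The best defence is that the section describes non-disclosure: nobody tells participants their arm, and neither arm knows the schedule. Controls and non-alerted intervention participants have nothing to compare their own experience with, and many may stay unsure. The consent text, which would show what they could deduce, is not at hand. This stands. A reader might infer that the trial is simply open-label, or that every alerted participant knows the arm. The documents do not support either: allocation is withheld, and an alert is a strong cue, not a disclosure. The defence does not rescue the sentence, however, which asserts for all participants something that the described contacts undermine.

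A second tempting step is to assume a reporting shift and set it against 0.15 SD. That has no basis in the documents. The direction is open too: attention could raise scores, while being told that one's scores are critical could lower them.

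A third objection is that Limitations already covers participants learning to avoid calls and judges it unlikely. Month-12 answers trigger no call in any case, since only months 1, 3 and 6 are screened. That weakens this one mechanism. It does not deal with reporting influenced by attention, expectation or knowledge of earlier critical scores.

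Finally, the support call applies to both arms, and the protocol does not say that assistants fill in answers. It would be too much to infer that staff administer the outcome. What remains is that they are unblinded and may be in contact at that moment.

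**Conclusion.** The blinding statement is wrong as written. After discharge, participants are not told their allocation, but intervention participants, and alerted ones above all, can infer it from contacts that controls do not receive. Study assistants are unblinded. The design therefore does not rule out reporting bias in the PROM part of the primary composite or in four of the five groups of secondary outcomes. Its size and direction are unknown.

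The conclusion rests on the described contacts alone and needs no assumed bias or alert rate. It does not extend to the inpatient stay, where allocation has not yet taken effect, or to concealment up to discharge. Nor is it a criticism of running the trial unmasked, because an intervention made of calls and reports cannot realistically be masked. The fault is that a safeguard is claimed which the design lacks, and that Limitations is silent about it.

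**What to change.** 1. Replace the sentence in Randomization and blinding with: *Allocation is concealed until after the discharge questionnaire; thereafter participants are not told their allocation but can infer it from the intervention contacts and are not effectively blinded, and study assistants are unblinded.*

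2. Add reporting bias in the PROMs, of unknown size and direction, to Limitations.

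3. Report claims-based and clinical outcomes (re-operations, readmissions, costs) separately from the composite, as results not subject to self-report bias. Take them from sources recorded in the same way in both arms. Note that care-seeking may still differ between the arms as part of the intervention's effect. Note also that claims are expected for about 2,700 patients, against about 10,500 completing all follow-ups.

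Restricting the PROM analysis to questionnaires completed without help is not recommended. It conditions on behaviour after randomization and leaves awareness of the arm untouched. Recording the completion mode at month 12 is optional and would be descriptive only.

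The cost is two changes of wording and a separate presentation of results already planned for collection. Randomization, sample size and data collection do not change.
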